### Study from the participant’s point of view

The study design from the participant’s point of view is depicted in Fig. 2. The standard procedure at the CPP is that patients are listed on a waiting list after a diagnostic screening phone call. Then, they will be contacted by the study team and receive verbal and written information on the study.

**Fig. 2 Fig2:**
[figure not shown]
Study design from the participant’s point of view

Twice a year, a new group of trainee therapists at the CPP starts their outpatient therapies. Consequently, trainees receive verbal and written information on the study there. Trainees who participate in the study will then participate in the two mindfulness workshops described above.

The information given to the participants of the study includes a precise description of the inclusion and exclusion criteria, information concerning the interventions, questionnaires, and the data-collection procedure. Furthermore, it will be emphasized that study participation is on a voluntary basis and that there is the option to revoke consent to participate in the study at any time without having to cite reasons or suffer disadvantages. Moreover, participants have the opportunity to instruct the study team to delete their data without providing reasons.

### Statistical analysis

We will compare baseline descriptive statistics between the three study arms with *χ*^2^-tests (for categorical variables) and with ANOVA / t-tests (for continuous variables).

In line with the recommendations of Baldwin, Imel, Braithwaite, and Atkins (Baldwin et al. 2014), we will apply a multilevel modeling approach to address the nested data structure (sessions at level 1 are nested within patients at level 2, which are nested within therapists at level 3): Thereby, we will treat time as a within-subject factor and treatment condition as a between-subject factor. We will analyze main effects, that is, differences in intercepts of TAU + M versus TAU + PMR versus TAU concerning process and outcome variables, and interactive effects, that is, differences in slopes of TAU + M versus TAU + PMR versus TAU concerning process and outcome variables (Raudenbush and Bryk 2002). Our statistical hypothesis implies that the intercept is significantly higher in the TAU + M than in the TAU + PMR and the TAU concerning both the process and outcome variables. Additionally, it implies that the slope increases significantly stronger in the TAU + M than in the TAU + PMR and the TAU concerning both the process and outcome variables. We will conduct analyses on the intention-to-treat sample as well as on the completer sample. Furthermore, patients’ and therapists’ pre-treatment characteristics will be investigated as outcome predictors at levels 2 and 3 to control for differential effects on outcome in the three treatment arms.

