**Methods/Design:**

To fill in this research gap, we designed the PrOMET Study. In our study, we will investigate the effects of brief, audiotape-presented, session-introducing interventions with mindfulness elements conducted by trainee therapists and their patients at the beginning of individual therapy sessions in a prospective, randomized, controlled design under naturalistic conditions with a total of 30 trainee therapists and 150 patients with depression and anxiety disorders in a large outpatient training center. We hypothesize that the primary outcomes of the session-introducing intervention with mindfulness elements will be positive effects on therapeutic alliance (Working Alliance Inventory) and general clinical symptomatology (Brief Symptom Checklist) in contrast to the session-introducing progressive muscle relaxation and treatment-as-usual control conditions. Treatment duration is 25 therapy sessions. Therapeutic alliance will be assessed on a session-to-session basis. Clinical symptomatology will be assessed at baseline, session 5, 15 and 25. We will conduct multilevel modeling to address the nested data structure. The secondary outcome measures include depression, anxiety, interpersonal functioning, mindful awareness, and mindfulness during the sessions.

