### Sample and ethics

A total of 30 trainee therapists and 150 patients will be recruited at the CPP. Enlisting as a trainee in the clinic is preceded by a rigorous assessment that evaluates the potential trainee’s personal suitability for becoming a CBT therapist.

The general inclusion criterion for patients is a primary depressive- or anxiety-disorder diagnosis in the Structured Clinical Interview according to the DSM-5 criteria (Falkai et al. 2014). We chose these two disorder groups because from patients being treated at German university therapy-training centers; approximately 40 % suffer from a primary major depression, and approximately 30 % suffer from a primary anxiety disorder (e.g. (Nelson and Hiller 2013)). Hence, our results will be of importance to a majority of outpatient diagnostic groups.

The general exclusion criteria for patients will be as follows: (1) an age below 18 or above 65 years, (2) insufficient German language skills, (3) those suffering from a psychotic disorder, (4) current suicidal risk. Comorbidities with disorders not on the exclusion list are generally not considered as limitations to entering the study, as long as depression and anxiety disorders are of primary concern.

Power analyses with G*Power (Faul et al. 2007) for the detection of small effects (Cohen’s *f* = 0.12) for the interaction between time (pre, mid-5, mid-15, post) and treatment condition (TAU-M versus TAU-PMR versus TAU) (ANOVA repeated measures, within-between-interaction, α = 0.05, power = 0.80, number of groups = 3, number of measurements = 4, pre-post correlation *r* = 0.05, nonsphericity correction = 1) along with practical clinical considerations (Flückiger 2014) resulted in a sample size of 123 patients. Taking potential dropouts into account, a total sample of 150 patients will be assigned to one of the three groups by a stratified randomization process. Patients will be stratified into one of two categories: one group with the main diagnosis of major depression and the other group with the main diagnosis of an anxiety disorder.

Voluntary participation and written, informed consent are necessary conditions for participation in the study. The local ethics committee (Ethikkommission der Fakultät für Verhaltens- und Empirische Kulturwissenschaften der Universität Heidelberg) approved the study protocol in accordance with the Helsinki Declaration.

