**Clinical assessment- patients**						
Structured Clinical Interview for DSM (SCID)	+				+	+
Brief Symptom Checklist (BSCL)	+		+	+	+	+
Inventory of Interpersonal Problems (IIP)	+		+	+	+	+
Beck Depression Inventory (BDI-II)	+		+	+	+	+
Beck Anxiety Inventory (BAI)	+		+	+	+	+
Scale for the Multiperspective Assessment of General Change Mechanisms in Psychotherapy-Patient (SACiP-P)			+	+	+	
Therapist techniques and study interventions (Interview by research team)					+	
Allegiance scale	+		+	+	+	+

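### The GSI model leaves the pre-treatment mean free in each arm with no baseline adjustment: the test is valid, but it forgoes precision that a common baseline mean would give

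*Protocol article*

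**What the plan says.** The abstract gives the schedule for the symptom outcome: "Clinical symptomatology will be assessed at baseline, session 5, 15 and 25". Table 1 shows a Pre wave for the BSCL and also for the BDI-II, BAI, IIP, GAF and patient KIMS. The WAI-SR is listed for sessions 1 to 25 only.

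The power calculation under Sample and ethics is for the "interaction between time (pre, mid-5, mid-15, post) and treatment condition", so the pre-treatment score is a response and one level of the time factor. The other inputs are "α = 0.05, power = 0.80, number of groups = 3, number of measurements = 4" and "pre-post correlation *r* = 0.05, nonsphericity correction = 1".

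Statistical analysis carries the same structure into the multilevel model: "we will treat time as a within-subject factor and treatment condition as a between-subject factor". It then says that differences between arms in both intercepts and slopes will be analysed, for process and outcome variables alike. Nothing in the article fixes a common pre-treatment mean or names the baseline score of the outcome as a covariate in the arm comparison. The nearest text says that pre-treatment characteristics of patients and therapists will be examined as outcome predictors. It does not name baseline GSI.

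**The concern.** With a separate intercept and slope for each arm, the pre-treatment mean of each arm is a free parameter, however time is coded. The treatment effect is then a difference in change from three separately estimated baselines. Patients are randomised, so if the pre score is unaffected by allocation, those baselines have the same expectation. Any observed difference between them is chance, and estimating three means instead of one passes that chance variation into every slope contrast.

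The time-by-condition contrast addresses the hypothesis on symptom reduction, and it is the effect used to size the trial. What is at stake is the precision of that contrast, using data the trial collects anyway.

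**Working it through.** **Inputs from the article:** f = 0.12, alpha 0.05, 3 groups, 4 measurements, nonsphericity 1, r = 0.05, calculated N = 123, planned N = 150, symptom waves at baseline and sessions 5, 15 and 25.

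**Assumptions added here:** equal correlation r between all waves; 50 patients per arm at N = 150; TAU + M separating from two equal control arms; several shapes of effect over time, since the article gives none.

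**1. The plan's own figure.** For the within-between interaction, λ = f² × N × m / (1 − r), with 6 and 3(N − 3) degrees of freedom.
- Printed r = 0.05: λ = 0.0144 × 123 × 4 / 0.95 = 7.46, power 0.489. Power of 0.80 needs N = 227 (228 with equal arms). The stated 123 is not reproduced.
- r = 0.50: λ = 7.085 / 0.50 = 14.17, power 0.810. Power of 0.80 needs N = 121, or 123 with equal arms. The stated 123 is reproduced.

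The main results therefore use r = 0.50, as an assumption. The mismatch between the printed r and N is a separate matter.

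**2. Effect of a common baseline mean.** Let d be the pattern of arm separation at sessions 5, 15 and 25. The covariance of the three change scores is proportional to I + J, and that of the three post scores given baseline is proportional to I + rJ, with the same factor (J is the matrix of ones). Hence λ is multiplied by

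d′(I + rJ)⁻¹d / d′(I + J)⁻¹d, where (I + aJ)⁻¹ = I − [a / (1 + 3a)]J.

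For an effect linear in session, d = (5, 15, 25), d′d = 875 and (sum of d)² = 2025:
- free baselines: 875 − 2025/4 = 368.75
- common baseline, r = 0.5: 875 − 0.2 × 2025 = 470
- ratio: 470 / 368.75 = 1.275

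**3. Power of the 6-df test, r = 0.50, N = 123 (free baselines: 0.810)**

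| Effect pattern | λ ratio | Power, common baseline | Gain (points) |
|---|---|---|---|
| Session 25 only | 1.067 | 0.839 | 2.9 |
| Early, then fading | 1.164 | 0.874 | 6.4 |
| Linear in session | 1.275 | 0.906 | 9.6 |
| Half at session 5, full from session 15 | 1.455 | 0.943 | 13.3 |
| Constant from session 5 | 1.600 | 0.963 | 15.3 |

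At N = 150 the linear case goes from 0.892 to 0.958. A simulation of the linear case at N = 123 (8,000 runs) gave 0.817 with free baselines and 0.906 with the post scores analysed given baseline. Type I error was about 0.05 for both.

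**4. The 2-df slope test.** Statistical analysis speaks of differences in slopes, which is a 2-df test if time is linear. With the same linear effect and r = 0.50, power goes from 0.929 to 0.974 at N = 123 (4.5 points) and from 0.968 to 0.991 at N = 150 (2.3 points). The gain is smaller because power is already high.

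**5. Pairwise slope contrast, 50 per arm, r = 0.50.** The standard error falls from 0.184 to 0.163 (SD units over 25 sessions). The variance ratio is 0.78, a fall of about 22%. A contrast with 80% power would rise to (1.960 + 0.842)/√0.785 − 1.960 = 1.20, that is about 88%. With an added random slope (assumed variance 0.25 SD² at session 25) the ratio is 0.83 and 80% becomes about 87%.

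**6. Dependence on r.** For the linear pattern, 6-df test and N = 123, the gain is 20 points at r = 0.30 (0.641 to 0.842), 9.6 at 0.50, 5 at 0.60 (0.900 to 0.950) and 1.5 at 0.70 (0.970 to 0.985).

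**The case against.** The strongest reply is that this is a choice between two valid models. A time-by-condition multilevel model with baseline as a response is conventional and unbiased under randomisation, and the 80% power was planned for that free-baseline test. This stands.

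A reader might infer that the trial loses about 10 points of its planned power. The documents do not support that. The figure needs a correlation the article does not print, an effect linear in session, the 6-df test and N = 123. It is also measured against a better model, not against the plan's own target. Nor should the printed r = 0.05 be used to enlarge it (0.489 to 0.860 in the linear case), because that value does not yield the stated sample size.

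A second reply is that the pre-treatment characteristics to be examined as predictors could include baseline GSI, and that a full analysis plan may settle the matter. The first part is possible but not stated, and entering a predictor would not by itself remove the separate baseline mean of each arm. On the second, the article does more than stay silent: it states separate intercepts and slopes by arm for outcome variables.

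A third reply is that equal baseline means do not follow simply from randomising before treatment. This also stands. The text does not say whether the pre score is taken before allocation is disclosed, and treatment conditions are not blinded. If patients knew their arm when they completed the pre questionnaire, the common-mean constraint could itself mislead.

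**Conclusion.** The point holds as one of forgone efficiency. For GSI, and for the secondary outcomes with a Pre wave, the plan gives each arm its own free pre-treatment mean and does not adjust the arm comparison for baseline. Every pattern and correlation examined favours a common baseline mean. At an assumed r of 0.5 the size is modest for the slope test and moderate for the 6-df test, and it shrinks as r rises.

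These figures rest on equal correlation between waves, on TAU + M separating from two equal controls, and on a pre score unaffected by allocation. A reader might go further and call the planned analysis biased or underpowered on this account. Neither follows: the estimator is unbiased over randomisations, and its power target was set for this very test. The change is worth making because it is cheap.

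**What to change.** In Statistical analysis, for GSI and each secondary outcome with a Pre wave, state that the multilevel model has one pre-treatment mean common to the three arms: time and time-by-condition terms, no condition effect at baseline, and the planned patient and therapist random effects kept. Report TAU + M versus TAU + PMR and TAU + M versus TAU as differences in slope or at session 25. State that the pre score is taken before allocation is disclosed. If it is not, the constraint needs to be reconsidered.

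Modelling sessions 5, 15 and 25 with the baseline score as covariate is acceptable only if the contrast is the adjusted arm difference, for example at session 25. It is not a substitute if the contrast is the slope from session 5 to 25, because any effect arising before session 5 would move into the intercept. This form also drops patients with no post-baseline score, whereas the common-mean model keeps them.

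The cost is a short change of wording, with no new patients, visits or data. The intercept hypothesis at baseline is no longer tested for these outcomes, so that sentence must be limited to match. Nothing is lost by this if the pre score precedes allocation.

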### Blinding, allegiance, and randomization

The focus of the current study is on the external validity and generalizability of the results to routine clinical practice. Consequently, according to the extension of the CONSORT statement concerning the criteria of a pragmatic randomized, controlled trial (Zwarenstein et al. 2008), no blinding concerning treatment conditions will be implemented in the current study. All participants will be informed about the general aims and procedures of the study. However, they will be blind concerning the specific hypotheses.

In our study, we will apply a crossed-therapist design in which a given therapist delivers the experimental and control conditions (Falkenstrom et al. 2013). This design includes specific limitations (e.g., the increased problem of allegiance effects (Falkenstrom et al. 2013)), but will be necessary to conduct the study in routine care. To address the potential problems of this design, we will control for allegiance effects with a specific instrument. Furthermore, all three treatment conditions will be introduced in a neutral way, and preparation in PMR will be as intensive as mindfulness preparation. Additionally, the crossed-therapist design allows researchers to address the issue of potential therapist effects (Baldwin and Imel 2013). More specifically, as efficacy varies across therapists, a crossed-therapist design allows researchers to control for these effects as the same therapists perform all of the different treatment conditions.

Treatment allocation will be performed by a blocked and stratified randomization process with a computerized random-number generator (www.random.org). Patients will be stratified according to their main diagnosis (depression or anxiety disorder) and then randomized by a balanced blocking procedure into the three treatment arms. Randomization will be conducted by an independent research assistant, while the other researchers have no access to the randomization list and process. According to the CONSORT statement (Altman et al. 2001), the people involved in the generation and implementation of the random treatment sequences will be completely separated. A CONSORT flow chart of the study design is depicted in Fig. 1.

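### Randomisation is stratified by main diagnosis, but the described model does not commit to including it; if diagnosis is prognostic, tests of arm differences in level would be somewhat conservative

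*Protocol article*

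**What the plan says.** Two sections of the protocol article fix the stratification. Sample and ethics: "Patients will be stratified into one of two categories", namely a main diagnosis of major depression or of an anxiety disorder. Blinding, allegiance, and randomization: "Patients will be stratified according to their main diagnosis (depression or anxiety disorder) and then randomized by a balanced blocking procedure into the three treatment" …, so allocation is blocked within diagnosis.

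Statistical analysis describes a three-level model ("sessions at level 1 are nested within patients at level 2, which are nested within therapists at level 3") in which "we will treat time as a within-subject factor and treatment condition as a between-subject factor". Two kinds of arm effect are tested: "differences in intercepts of TAU + M versus TAU + PMR versus TAU" and "differences in slopes of TAU + M versus TAU + PMR versus TAU".

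Covariates come up in two places, and neither names main diagnosis:
- Statistical analysis adds that patients' and therapists' "pre-treatment characteristics will be investigated as outcome predictors at levels 2 and 3", with the aim of controlling for differential effects on outcome across the arms. The characteristics are not listed.
- Bias minimization, patient (in the Discussion) lists variables to be tested as possible confounders: psychiatric comorbidity, age, sex, and earlier and current mindfulness or PMR practice.

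**The concern.** Blocking within diagnosis balances the two diagnostic groups across the three arms. Differences between the groups therefore contribute almost nothing to the real sampling variation of an arm contrast. A model without diagnosis still counts those differences as unexplained patient variance, so its standard error is larger than the real one. The test then rejects too rarely under the null and gives up some of the precision that stratifying was meant to provide.

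This bears mainly on comparisons of level. The first hypothesis in Objectives concerns the level of alliance. Table 1 schedules the WAI-SR at sessions 1 to 25 with no pre-treatment value, so the level contrast carries much of that hypothesis.

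The described analysis also leaves open whether diagnosis is adjusted for, and that choice should not be made after results are seen.

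**Working it through.** **Inputs from the protocol article.** Three arms; two strata; 123 patients from the power calculation, with 150 to be recruited; about 40% primary depression and 30% primary anxiety disorder among comparable training-centre patients.

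**Assumed inputs.**
- Stratum mix p = 4/7 to 3/7, from 40:30. In 123 patients this is 70:53.
- Block size 6 (none is given).
- d, the difference between diagnostic groups in within-stratum SDs of the patient-level outcome. The documents give no value, so a range from 0 to 1 is shown.

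**The plan's own figure.** The article gives no figure for the effect of diagnosis, so there is none to reproduce on this point. The 123 is used only as a sample size. It does not follow from the printed repeated-measures correlation of 0.05, which gives 48.9% power at 123. It does follow from 0.5, which gives 81.0% with equal groups. That is a separate matter: the standard-error ratio below does not contain N.

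**Step 1: level contrasts.** With p(1−p) = 12/49 = 0.245,

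SE without diagnosis / SE with diagnosis = √(1 + p(1−p)d²).

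- d = 0.5: √(1 + 0.245 × 0.25) = √1.061 = 1.030
- d = 0.8: √(1 + 0.245 × 0.64) = √1.157 = 1.076

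The approximate true size of a nominal 5% test is 2(1 − Φ(1.96 × ratio)): 4.3% at d = 0.5 and 3.5% at d = 0.8.

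This was checked by simulating 123 patients, 6,000 runs per setting. The Monte Carlo standard error of a 5% rejection rate is √(0.05 × 0.95/6000) = 0.28 points. Power is for a contrast of 0.62 SD, which has about 80% power with the diagnosis term.

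| d | SE ratio, formula | SE ratio, simulated | True size without term | Power without / with term |
|---|---|---|---|---|
| 0 | 1.000 | 1.000 | 5.0% | not run |
| 0.2 | 1.005 | 1.005 | 5.2% | 78.7% / 79.0% |
| 0.3 | 1.011 | 1.011 | 4.7% | not run |
| 0.5 | 1.030 | 1.031 | 4.5% | 77.8% / 79.7% |
| 0.8 | 1.076 | 1.078 | 3.5% | 75.4% / 80.0% |
| 1.0 | 1.116 | 1.119 | 2.9% | 72.8% / 79.8% |

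The mechanism is visible at d = 0.8. Without the term, the model reports an SE of 0.238 against an empirical 0.219. With the term, the figures are 0.221 and 0.218.

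**Step 2: slope contrasts.** Data were simulated at four times (0, 5, 15 and 25 sessions, rescaled to 0–1), with intercept variance 0.5, slope SD 0.5 and residual variance 0.5. Each patient's least-squares slope was compared across arms, 3,000 runs per setting.
- Diagnosis shifts level only (0.5 or 0.8): SE ratio 1.000.
- Diagnosis also shifts the slope by 0.3: 0.2333/0.2310 = 1.010.
- Diagnosis also shifts the slope by 0.5: 0.2367/0.2303 = 1.028.

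The same formula explains these. The within-stratum variance of a fitted slope is 0.25 + 0.5/0.59 = 1.097 (SD 1.048), where 0.59 is the sum of squared deviations of the four times. The shifts are then d = 0.286 and 0.477, giving 1.010 and 1.028. A random intercept and slope model (20 runs per setting) agreed: slope ratios of about 1.00 with a level shift only, and 1.008 and 1.031 with the slope shifts. Only a diagnosis by time term recovered the loss; a main effect of diagnosis did not.

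**Limits.** The simulations have no therapist level. Because d is in SDs of the patient-level summary, the same raw difference counts for more where averaging over occasions shrinks that SD.

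**The case against.** The strongest reply is that this is a journal article. It names time and condition but nowhere says they are the only terms, and a full plan could list the stratification factor. Main diagnosis is itself a patient characteristic known before treatment, so it fits the sentence on level-2 predictors, which has a stated purpose of control. The reply stands to this extent: a reader might infer that diagnosis is excluded from the model, and the article does not support that. It neither includes nor excludes it. What remains is that the article discusses covariates twice, names the randomisation factor neither time, and treats predictors as a further step rather than as part of the arm comparison.

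A reader might also infer that the standard errors are bound to be too large. That requires diagnosis to be prognostic, and no document gives a figure for it. Near d = 0 nothing is lost.

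Nor do the level figures carry over to the time by condition interaction on which the trial was powered. The patient random intercept absorbs a pure level difference there. The symptom hypothesis concerns stronger reductions, which is a slope question, so the level argument applies chiefly to alliance. The documents give no reason to expect alliance to differ strongly between depression and anxiety.

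**Conclusion.** The point holds as a conditional one. The described analysis does not commit to the factor by which patients are randomised. If diagnosis is left out and is prognostic, tests of level contrasts are conservative. The SE excess is about 0–1% for a stratum difference of 0–0.3 SD, 3% at 0.5 SD and 8% at 0.8 SD. At the last two, true size is about 4.5% and 3.5%, and the power loss is about 2 and 4.6 points. Slope contrasts change only if diagnosis also predicts the slope, by about 1–3% in the settings tried.

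These sizes rest on the assumed d, stratum mix, block size and variance components. The omission can be read from the text with confidence; its size cannot. Estimates are not biased and type I error is not inflated, so this is an improvement available at no cost and not a threat to validity.

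**What to change.** In Statistical analysis, pre-specify main diagnosis (depression or anxiety disorder) as a fixed effect in the primary multilevel models for the WAI-SR and the GSI, and add diagnosis by time where slopes are compared. Keep the search for further patient and therapist predictors as a separate step labelled exploratory. If a full analysis plan already contains these terms, one sentence in the article saying so is enough.

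The cost is one or two model terms. Diagnosis is known for every randomised patient, so no data collection, sample size or trial procedure changes.

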### Objectives

The main purpose of this study is to identify whether exercises with mindfulness elements carried out at the beginning of individual therapy sessions help to improve the therapeutic process under effectiveness conditions. Consequently, we designed a study to analyze the effects of a 5-min session-introducing intervention with mindfulness elements (SIIME) conducted together by trainee therapists and their patients in a randomized, controlled, longitudinal design under naturalistic conditions with PMR as the active control group.

More specifically, we will examine the effects of SIIME practiced by both outpatients and CBT trainee therapists at the beginning of the 25 therapy sessions (brief-term CBT of the German healthcare system) on (a) therapeutic alliance measured on a session-to-session basis and (b) on clinical outcomes assessed every 10 sessions. Thus, before the start of therapeutic treatment, patients are randomized into a treatment-as-usual + mindfulness intervention group (TAU + M) practicing SIIME, a TAU + PMR-control group practicing a session-introducing short form of PMR, or a TAU control group without standardized session-introducing intervention. Before the start of the intervention study, all therapists will participate in a 6-week workshop-based mindfulness and PMR program. We will investigate the following hypotheses:We hypothesize that both patients and therapists of the TAU + M will experience higher levels of therapeutic alliance compared to the TAU + PMR and TAU.We hypothesize that in the TAU + M, there will be stronger reductions in clinical symptomatology of patients compared to the TAU + PMR and TAU.

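### The statistical hypothesis predicts higher intercepts and steeper increases for every outcome, which is the wrong direction for the symptom scores, including primary outcome 2

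*Protocol article*

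**What the plan says.** Under Objectives, the protocol article gives two hypotheses. The first is that alliance will be stronger in the mindfulness arm than in both control arms. The second is that "in the TAU + M, there will be stronger reductions in clinical symptomatology of patients compared to the TAU + PMR and TAU".

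Under Primary outcome measures, alliance is the WAI-SR (primary outcome 1) and symptoms are the Global Severity Index (GSI) of the BSCL (primary outcome 2), an index of symptom severity.

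Under Statistical analysis, the three-level model yields two kinds of contrast. The first is described as follows: "We will analyze main effects, that is, differences in intercepts". The second is the difference in slopes. The direction is then fixed: "Our statistical hypothesis implies that the intercept is significantly higher in the TAU + M" than in both control arms. The next sentence adds that "it implies that the slope increases significantly stronger in the TAU + M than in the TAU + PMR and the TAU". Both sentences apply to process and outcome variables together, and neither makes an exception or reverses the sign for symptom scores.

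The section does not say where time is zero. By Table 1, the BSCL is given at Pre, Mid-5, Mid-15, Post and follow-up, and the WAI-SR at sessions 1 to 25 with no Pre value. Under Sample and ethics, the sample size is based on the time-by-condition interaction, with alpha 0.05 and power 0.80. No one-sided test is stated.

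**The concern.** The paragraph on the statistical hypothesis is the only place where the article says what pattern of results would support the two clinical hypotheses. It uses one direction for all variables. That direction suits alliance, and it suits GAF and KIMS, where higher is better. It does not suit a severity score. Taken literally, a symptom result that meets the criterion is one in which the mindfulness arm did no better, or did worse, on a primary outcome. Taken loosely, the sign, the time origin and the choice between intercept and slope are left to be settled at analysis.

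The intercept part has a second difficulty. The GSI is first measured before treatment, so under the usual coding the intercept is a pre-treatment quantity. Calling a difference in it a main effect invites a chance imbalance to be read as an effect of treatment.

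**Working it through.** The plan gives no figure for this point, so there is none to reproduce. The check compares the stated directions and then asks what each contrast would show if the treatment worked.

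**1. Directions side by side**

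| Outcome | Better score | Objectives predict for TAU + M | Statistical analysis predicts for TAU + M |
|---|---|---|---|
| WAI-SR (primary 1) | higher | higher | higher intercept, steeper increase: agrees |
| GSI (primary 2) | lower | larger reduction | higher intercept, steeper increase: contradicts |
| BDI-II, BAI, IIP | lower | larger reduction, as symptom measures | higher intercept, steeper increase: contradicts |

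The better direction for the symptom scales follows from what they measure: severity, depressive symptoms, anxiety symptoms and interpersonal problems.

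**2. Slope contrast on the GSI**

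Take one comparison of TAU + M with a control arm, tested two-sided at 0.05. Let the true benefit give 80% power, that is, a standardised effect of 2.8 towards lower scores.

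- Significant in the beneficial (lower) direction: Φ(2.8 − 1.96) = Φ(0.84) = 0.80.
- Significant in the stated (higher) direction: Φ(−1.96 − 2.8) = Φ(−4.76) ≈ 0.000001.

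**3. Intercept contrast on the GSI, for any time origin**

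Write the mean difference, TAU + M minus control, at session t as D(t) = d0 + d1·t, with t = 0 at Pre. Randomisation makes d0 = 0, and benefit means d1 < 0. If time is coded zero at session c, the intercept contrast is D(c) = d1·c.

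- Origin at Pre (c = 0): the contrast is 0. Significance in the higher direction is pure chance, 2.5% per comparison at two-sided 5%.
- Any later origin (c > 0): the contrast is negative under benefit. A higher intercept then points to harm.

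**4. Numerical illustration**

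The assumed values, none of them from the documents, are: two arms of 50; measurements at sessions 0, 5, 15 and 25; a GSI fall of 0.6 against 0.2 over 25 sessions; between-patient intercept SD 0.6; slope SD 0.015 per session; residual SD 0.25; 4,000 simulated trials per origin. Here d1 = −(0.6 − 0.2)/25 = −0.016 per session. The mean measurement time is (0 + 5 + 15 + 25)/4 = 11.25.

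| Time zero at | True intercept contrast | Significantly higher | Significantly lower |
|---|---|---|---|
| Pre | 0 | 2.4% | 2.6% |
| Mean time, 11.25 | −0.016 × 11.25 = −0.18 | 0.03% | 29% |
| Session 25 | −0.016 × 25 = −0.40 | 0% | 76% |

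The slope contrast was significantly lower in about 98% of trials for each origin, and never significantly higher.

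**5. Alliance**

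The WAI-SR has no Pre value. If time is zero at session 1, the intercept contrast is the difference after one 5-minute exercise. If time is centred at the midpoint, (1 + 25)/2 = session 13, then under a linear course it is the average difference over sessions 1 to 25, which is closer to what the first hypothesis asserts. The direction is right either way, but the meaning depends on an origin that the article does not give.

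**The case against.** The strongest reply is that the analysis survives the wording. The model includes a condition-by-time slope contrast, the sample size was set for that interaction, and no one-sided test is stated. Objectives gives the intended direction plainly. A two-sided slope test would pick up a larger reduction whatever the prose predicts. All of this stands. A reader might infer that the trial cannot confirm its symptom hypothesis, but the documents do not support that. Only the directional criterion as written fails.

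A second reply is that the time origin is a detail that an article may leave to the full protocol or analysis plan. Calling intercept differences main effects could also mean a contrast of average levels, especially as the section plans a separate baseline comparison of the arms. This stands too. A reader might infer that the plan definitely counts a baseline difference as a treatment effect, or that the alliance test definitely concerns session 1. Both hold only under a coding that the article does not state. For the GSI, however, no coding rescues the criterion, because step 3 shows that a higher intercept is never the mark of benefit.

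A charitable reader might take the steeper slope to mean faster improvement. That could repair the slope sentence, but it does not repair a higher intercept on a severity score.

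**Conclusion.** The point holds for direction. For the GSI, and for BDI-II, BAI and IIP, the stated statistical hypothesis contradicts the symptom hypothesis under Objectives, and the intercept criterion cannot show benefit on these scores under any time coding. The wording is right for WAI-SR, and also for GAF and KIMS.

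The planned slope contrast is sound once its sign is corrected. That a pre-treatment difference would be read as an effect, and that alliance would be judged at session 1, are conditional on the unstated time origin.

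No inflated error rate or loss of power can be attached to this. The article does not say explicitly whether intercept, slope or both must be significant, so any such figure would rest on an invented rule.

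The intercept argument assumes a linear course and Pre scores unaffected by allocation. If a straight line were fitted to a benefit that emerged late, the fitted value at Pre could come out above zero, but that would be misfit and not evidence of benefit.

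**What to change.** Rewrite the paragraph on the statistical hypothesis so that the direction is given for each outcome.

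- **GSI, BDI-II, BAI and IIP:** rest the hypothesis on the condition-by-time contrast, TAU + M minus control below zero, against each control arm. State that an intercept difference does not count as a treatment effect. Preferably fit a common baseline mean across arms. That is an improvement and is not needed to remove the contradiction.
- **WAI-SR:** keep the prediction of higher values. State the time origin, for example centred at session 13, so that the condition effect is the alliance level over sessions 1 to 25. Other origins are possible if stated and justified in advance.

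The cost is one reworded paragraph and a change in model coding. No new data, visits or patients are needed.
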